### Cross-sectional surveys: chemical analysis

Samples of the three types of LNs will be subjected to chemical residue analysis at the WHO Collaborating Centre for quality control of pesticides (Gembloux, Belgium) at the beginning of the trial (t0) to ensure that the target dose of deltamethrin is correct and at yearly intervals (t12, 24 and 36) to facilitate interpretation of bioassay data. From the 30 LNs sampled for bioassays at t12 and t24 months and the 50 LNs sampled at t36 months, additional 30 × 30 cm sections will be cut from positions 2–5 (Fig. 3) to estimate total deltamethrin content in the net (expressed in both g/kg and mg/m^2^). Samples will be rolled up and wrapped in labelled, aluminium foil and stored at 4 °C, prior to extraction of deltamethrin and analysis by GC according to the Collaborative International Pesticides Analytical Council (CIPAC) protocol [36].

### Cross-sectional surveys: fabric integrity

At t6, 12 and 18 months post LN distribution, the 30 LNs destructively sampled for bioassays will be scored for physical integrity by draping the nets over a frame and counting the number and types (due to burning, tearing, split seams or animal damage) of holes of different sizes according to location on the net (top, upper side, lower side). Holes greater than 0.5 cm will be classified into the following categories: smaller than a thumb (0.5–2 cm); larger than a thumb but smaller than a fist (2–10 cm); larger than a fist but smaller than a head (10–25 cm) and larger than a head (>25 cm). At t24 and 36, physical integrity of the nets will be evaluated for a randomly selected sample of 100 LNs of each brand (including the 30 destructively sampled for bioassays). Net integrity (hole index, hole area and circumference) of each net type will be calculated as per WHO guidelines [28] (Table 3). In addition, any evidence of repairs and types of modification will be recorded.

**Table 3 Tab3:** LN hole size index

Hole Size Categories (cm)	Hole Diameter^a^ (*d;* cm)	Hole radius (*r* = *d/*2)	Hole Area^b^ (π**r* ^2^)	Hole Index^c^
0.5–2.0	1.25	0.625	1.23	1
2–10	6	3	28.28	23
10–25	17.5	8.75	240.56	196
>25	30	15	706.95	576

^a^Weights for each size category were estimated assuming that the average hole diameter was the midpoint in each category, except for the largest hole where the average diameter was assumed to be 30 cm

^b^The approximate area of an average sized hole from each category was estimated by assuming each hole was approximately circular

^c^Final weights for each size category were then estimated by dividing the area encompassed by a hole in the smallest size category (i.e. 1.23)

### Cross-sectional surveys: fabric strength

At t6, 12, 18, 24, 30 and 36 months post LN distribution, when 30 LNs of each brand are destructively sampled for bioassays, the remaining part of each net will be packaged and sent to CITEVE, Portugal to conduct a series of tests to determine the strength of netting fabric and resistance-to-damage as recommended by the WHO consultation on the determination of fabric strength of LNs [37]. These tests will include bursting strength (pneumatic), wounded bursting strength, hook tensile strength, snag strength, abrasion resistance and hole propagation tests. These measures of snagging, tearing, holing and hole enlargement will be correlated with measures of net durability and hole index during 3 years of household use.

### Cross-sectional surveys: community practices

At t6, 12, 18, 24, 30 and 36 months post LN distribution, one adult participant from each of 90 of the households selected for fabric integrity surveys (30 per study arm), will be interviewed to assess net utilization practices (including early morning observations), method and number of washes and type of soap used, as per the standard WHO LN durability monitoring questionnaire [28].

### Cohort study: household survivorship and fabric integrity

To measure LN household survivorship and attrition, a longitudinal cohort of 250 LNs from 125 randomly selected households (two nets per household) will be followed at t6, 12, 18, 24, 30 and 36 months post LN distribution. At each time point, 150 of the LNs (the higher of the 2 ID codes per house) will be examined to measure the loss of fabric integrity over time (hole index, as above) and net hanging (net usage), and attrition (physical presence/absence of the nets) of all household LNs will be assessed. When a LN is missing from a house, the participants will be questioned to determine the reason for its loss or absence, which will be categorised as: loss by giving away the LN to others, sold, stolen, mislaid, using for alternative purposes or discarded due to loss of integrity (wear and tear); the latter is most important for assessing the relative durability of each type of net. LN owners will be requested to retain and store the net if they stop using it and to allow its inspection during follow up surveys. At the end of the 3 year trial period, study nets will be replaced on their production regardless of condition. Study LNs in the house that have never been used will be recorded but excluded from the analysis.

In contrast to the cross-sectional surveys, where only surviving LNs will be examined, the cohort study will allow gradual deterioration of individual LNs to be monitored, and the point at which the net is discarded or no longer used, determined. Households participating in the cohort study will not be sampled during cross-sectional surveys.

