### Sample size rationale

Sample size calculations are based on detecting differences in LN insecticide efficacy and physical durability (attrition rate and fabric integrity) between the three comparison nets over a 3 year period, while allowing for destructive sampling and replacement of LNs for biological and chemical efficacy assays and an expected attrition rate of 20% per year for each product.

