#### Cross-sectional surveys: biological and chemical efficacy and fabric integrity

During cross-sectional surveys, one LN will be sampled from 30 households per study arm per survey at t0, 6, 12, 18, 24 and 30 months and from 50 households at 36 months, thus requiring a minimum of 320 households per intervention arm, factoring in an attrition rate of 20% per year (total of 960 households). Allowing for distribution of 3.2 nets per house (universal coverage of participating households) plus replacements at the time of net withdrawal for bioassays/chemical assays and possible attrition in use, the total number of LNs required is 1634 per study arm. To assess fabric integrity, a total of 50 LNs will be destructively sampled per arm per survey; 30 of these will be the same nets collected for bioassays.

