#### Cohort surveys: household survivorship and fabric integrity

During the longitudinal cohort study, 250 LNs from 125 households per study arm will be monitored after 6 months and then followed at annual intervals to evaluate net survivorship and attrition and loss of fabric integrity over 3 years. All 250 LNs will be assessed for survivorship and 150 (approximately one per household) will be examined for loss of fabric integrity. Assuming an attrition rate of 20% per year, 200 households will participate in the cohort study (an additional 640 LNs), allowing a 12% point difference in LN attrition rate to be detected.

A total of 2300 nets per study arm will be required for both cross-sectional and cohort surveillance.

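### The cohort's one-net-per-house rule does not deliver the stated 150 hole-scored nets per arm at each survey: 125 households give at most 125, and 200 households leave about 80-102 at month 36 before stored nets are counted

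*Protocol article*

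**What the plan says.** The Methods section on the cohort study sets the size and the selection rule. It says "a longitudinal cohort of 250 LNs from 125 randomly selected households (two nets per household) will be followed" and then, for hole scoring, "At each time point, 150 of the LNs (the higher of the 2 ID codes per house) will be examined". It lists surveys at months 6, 12, 18, 24, 30 and 36, and gives as the cohort's purpose that the deterioration of individual nets can be watched over time.

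The sample size section on the cohort makes the figures per arm ("250 LNs from 125 households per study arm will be monitored after 6 months") and describes the hole-scored subset as "150 (approximately one per household) will be examined for loss of fabric integrity". It then adds the allowance for losses: "Assuming an attrition rate of 20% per year, 200 households will participate in the cohort study (an additional 640 LNs), allowing a 12% point difference". That difference refers to the attrition rate. The sample size rationale assumes "an expected attrition rate of 20% per year for each product".

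Three other places bear on the count:
- The cohort section asks owners to store nets they stop using and to allow inspection. The data analysis section counts nets kept for inspection but out of use through poor integrity as lost to attrition.
- The section on withdrawals replaces owners who withdraw, or who leave the area with their nets, by another net user in the hamlet.
- The sample size section has the cohort seen after 6 months and then yearly. Table 1 agrees, with no cohort survey at months 18 or 30.

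**The concern.** For survivorship, a lost net is an outcome event and costs no sample. For hole scoring it is different: a net that is no longer in the house cannot be examined. If one net per house is designated by its ID code, each such loss removes an observation. The 150 then has to be covered by the number of households enrolled and the allowance for losses, and on the stated figures it is not.

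The Discussion calls the trial primarily a comparison of field durability, and cohort hole index is one of its main measures of this. The stated sample size for that outcome is therefore wrong on the plan's own inputs, and the shortfall is largest at month 36. Meanwhile the second cohort net in each visited house goes unscored.

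**Working it through.** **Inputs.** 150 nets per survey, one per house by the higher of two ID codes; 125 households with two nets each (cohort section; per arm from the sample size section); 20% attrition per year; 200 households and 640 nets after the allowance. I read the 200 as per arm, because 1634 + 640 = 2274, close to the 2300 nets per arm that the article states.

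**Reproducing the 200.** 125 x (1 + 3 x 0.20) = 125 x 1.6 = 200 households. The 640 follows from the cross-sectional sample size section ("Allowing for distribution of 3.2 nets per house (universal coverage of participating households"): 200 x 3.2 = 640. Both are exact. To keep 125 after losses one divides by the retained fraction instead:
- compounding: 125 / 0.8^3 = 125 / 0.512 = 244.1, so 245 households;
- linear: 125 / (1 - 0.60) = 125 / 0.40 = 312.5, so 313 households.

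**Before any loss.** One net per house from 125 households is at most 125, which is below 150.

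**After losses.** The article does not say whether 20% per year compounds, so both forms are shown. Retained fraction at month t: 0.8^(t/12) (compounding) or 1 - 0.2t/12 (linear). Entries are compounding / linear, per arm.

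| Month | One net, 125 houses | One net, 200 houses | Both nets, 200 houses (400 at start) |
|---|---|---|---|
| 6 | 111.8 / 112.5 | 179 / 180 | 358 / 360 |
| 12 | 100 / 100 | 160 / 160 | 320 / 320 |
| 18* | 89.4 / 87.5 | 143 / 140 | 286 / 280 |
| 24 | 80 / 75 | 128 / 120 | 256 / 240 |
| 30* | 71.6 / 62.5 | 114 / 100 | 229 / 200 |
| 36 | 64 / 50 | 102 / 80 | 205 / 160 |

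*A cohort survey only under the six-monthly schedule.

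With 200 houses the count is first below 150 at month 18 on the six-monthly schedule, or at month 24 on the annual one. Holding 150 such nets at month 36 would take 150 / 0.512 = 293 or 150 / 0.40 = 375 households per arm.

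**Stored nets added back.** The article gives no share of attrition that stays inspectable. Its Discussion offers two guides. In the Cambodian trial, twice as many nets went for other reasons as for integrity, so 1/3 of losses were for integrity. In the Tanzanian evaluation, 32% failed on integrity and 52% were absent for other reasons, so 32/84 = 38%. Assuming that every such net is stored and produced, for 200 houses:
- month 24, compounding: 128 + 72 x (0.333 to 0.381) = 152 to 155; linear: 120 + 80 x (0.333 to 0.381) = 147 to 150;
- month 36, compounding: 102.4 + 97.6 x (0.333 to 0.381) = 135 to 140; linear: 80 + 120 x (0.333 to 0.381) = 120 to 126.

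To reach 150 at month 36, (150 - 102.4)/97.6 = 49% (compounding) or (150 - 80)/120 = 58% (linear) of lost nets would have to be inspectable or substituted.

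**The case against.** A reader might infer that 150 can never be reached and that 80-102 nets are what the field team will find. The article does not support either statement.

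- Stored nets are attrition by definition but can be scored, so 80-102 is a floor. On the assumption above, stored nets roughly close the gap at month 24, though not at month 36.
- The article never says that lost nets go unreplaced. Owners who withdraw or move away are replaced. That rule does not reach nets that were sold, stolen, given away or thrown out, and nothing says how 150 is kept up.
- The sample size section says only approximately one per household, and 640 cohort nets are issued. Of these, 640 x 0.512 = 328 or 640 x 0.40 = 256 remain at month 36, so 150 is reachable if any of them may be scored. If the rule means the higher-numbered net still present out of two, and losses are independent, 200 x (1 - 0.488^2) = 152 houses (compounding) or 200 x (1 - 0.6^2) = 128 (linear) hold one. Either reading changes which net is scored over time, which fits poorly with following individual nets, and neither is written down.

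A reader might also infer a stated loss of power. The article gives no power for hole index; its 12-point difference concerns attrition. No power loss can be derived from it. Nor is the cohort the only source of month-36 integrity data. The cross-sectional fabric integrity section scores 100 nets per brand at months 24 and 36 (the sample size section says 50), although the article notes that those surveys see only surviving nets.

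What stands is that the stated 150 at each time point does not follow from the stated rule, households and attrition.

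**Conclusion.** The point holds for the rule as written. The stated size exceeds what 125 households can supply at the outset. From 200 households it falls to 160 at month 12, 120-128 at month 24 and 80-102 at month 36 before stored nets are counted. Under the assumed inspectable share, month 36 reaches about 120-140.

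This rests on one designated net per house, 20% yearly attrition applying to those nets, 200 being a per-arm figure, and no substitution beyond withdrawn or moved owners. The allowance to 200 is a multiplication where a division was needed. The fault is a misstated sample size for a main durability outcome, and it should be corrected. It does not invalidate the cohort or the survivorship analysis.

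**What to change.** Preferred: in the cohort study section, replace the one-net rule by hole scoring of both cohort nets in each of the 200 households at every cohort survey. That is 400 nets per arm at the start and about 160-205 at month 36 before stored nets. Account for clustering by household and hamlet in the analysis, since participating households in a hamlet receive the same net type. With only 125 households, both nets would leave 250 x 0.512 = 128 or 250 x 0.40 = 100, so this fix depends on following all 200.

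Alternative: keep one net per house and, in both cohort sections, replace 150 by the expected count by survey. At month 36 this is about 80-102 as a lower bound, or 50-64 if only 125 households are followed.

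In either case, reconcile 150 with 125 and 200 households, say whether a lost net is substituted and by which net, and reconcile the six-monthly cohort schedule with the annual one in the sample size section and Table 1.

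The cost is protocol wording and extra scoring time in houses already visited, with no new households or nets. Two nets in one house add less than two independent observations. With the trial in its second monitoring year, second nets scored from now on would lack earlier hole counts.

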### Adverse events monitoring

The frequency of adverse events (AEs) will be monitored among 100 randomly selected households from each of the three study arms using a structured questionnaire at 1 month following LN distribution. During these house visits, the study team will also assess LN usage rates and ensure LNs are being hung properly.

### Insecticide resistance monitoring

Susceptibility of *An. gambiae s.l.* and *An. funestus* to deltamethrin will be measured at baseline and annually throughout the monitoring period both in study villages and neighbouring areas without study LNs, using WHO susceptibility tests [38].

### Project oversight, safety considerations and handling withdrawals/drop-outs

There are no apparent risks to the safety of study participants and communities. All three products will be used in compliance with WHO recommended guidelines [26, 35, 39]. Project progress and any issues arising will be subject to annual review under the WHO Continuing Ethical Review process. While each brand of LN is expected to provide protection from malaria, participants will be informed that they should visit the nearest health facility or district hospital for diagnosis, upon experiencing fever or any other malaria symptoms. Additionally, the Principal Investigator (PI) will inform the DMO about possible reporting of AEs and to provide medical care, as necessary.

Participants and households are free to withdraw from the study at any time with impunity and will be allowed to retain their LNs. Net owners who have withdrawn consent, or moved out of the study area and have taken their LNs with them, will be replaced by another net user from the same or neighboring household within the hamlet.

### Sample size rationale

Sample size calculations are based on detecting differences in LN insecticide efficacy and physical durability (attrition rate and fabric integrity) between the three comparison nets over a 3 year period, while allowing for destructive sampling and replacement of LNs for biological and chemical efficacy assays and an expected attrition rate of 20% per year for each product.

#### Cross-sectional surveys: biological and chemical efficacy and fabric integrity

During cross-sectional surveys, one LN will be sampled from 30 households per study arm per survey at t0, 6, 12, 18, 24 and 30 months and from 50 households at 36 months, thus requiring a minimum of 320 households per intervention arm, factoring in an attrition rate of 20% per year (total of 960 households). Allowing for distribution of 3.2 nets per house (universal coverage of participating households) plus replacements at the time of net withdrawal for bioassays/chemical assays and possible attrition in use, the total number of LNs required is 1634 per study arm. To assess fabric integrity, a total of 50 LNs will be destructively sampled per arm per survey; 30 of these will be the same nets collected for bioassays.

#### Cohort surveys: household survivorship and fabric integrity

During the longitudinal cohort study, 250 LNs from 125 households per study arm will be monitored after 6 months and then followed at annual intervals to evaluate net survivorship and attrition and loss of fabric integrity over 3 years. All 250 LNs will be assessed for survivorship and 150 (approximately one per household) will be examined for loss of fabric integrity. Assuming an attrition rate of 20% per year, 200 households will participate in the cohort study (an additional 640 LNs), allowing a 12% point difference in LN attrition rate to be detected.

A total of 2300 nets per study arm will be required for both cross-sectional and cohort surveillance.

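### The cohort's size is given as 125 and as 200 households per arm and its hole-count sample as 150 nets; these do not fit together, so the 12-point detectable difference has no fixed sample

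*Protocol article*

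**What the plan says.** All places are in the protocol article.

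- **Methods, Cohort study: household survivorship and fabric integrity:** "a longitudinal cohort of 250 LNs from 125 randomly selected households (two nets per household) will be followed". For fabric integrity, "150 of the LNs (the higher of the 2 ID codes per house) will be examined". The same section also has the presence or absence of all nets in the household checked.
- **Sample size rationale, Cohort surveys:** "250 LNs from 125 households per study arm will be monitored after 6 months", the purpose being "to evaluate net survivorship and attrition and loss of fabric integrity over 3 years". Then: "Assuming an attrition rate of 20% per year, 200 households will participate in the cohort study". The paragraph adds 640 nets for these households, describes the 150 fabric-integrity nets as roughly one per household, and claims that a 12-point difference in net attrition can be detected.
- **Sample size rationale, opening paragraph:** the loss allowance is "an expected attrition rate of 20% per year for each product", which is a rate for nets.
- **Data analysis:** attrition is missing nets over nets distributed. Survivorship is nets present and in use over nets originally distributed and not given away.
- **Project oversight (withdrawals and drop-outs):** owners who withdraw consent, or who leave the area with their nets, "will be replaced by another net user from the same or neighboring household within the hamlet".

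**The concern.** The cohort carries the survivorship comparison, and the Discussion says that the trial is designed primarily to compare field durability. A reader cannot tell how many households and nets per arm make up this cohort. Both 125 and 200 households are stated, and nothing says whether the extra 75 are followed, analysed or neither.

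The allowance behind the 200 is also unclear in kind. The same word, attrition, names the planning loss and the outcome. A net that goes missing is an event in the attrition analysis, so its loss does not shrink that sample. A household that can no longer be observed does shrink it. The two call for different allowances, and the text does not separate them.

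At stake are a detectable difference that cannot be tied to a sample, a 36-month denominator still open to interpretation, and a replacement rule that, as written, could bring later substitutes into the cohort.

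**Working it through.** **1. Reproducing the 200.** Inputs: 125 households, 20% a year, 3 years.

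- 125 × (1 + 3 × 0.20) = 125 × 1.6 = 200, exactly.
- Other forms do not give 200: 125 / 0.8³ = 244.1; 125 / (1 − 0.6) = 312.5; 125 × 1.2³ = 216.

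The formula is therefore inferred, but the match is exact. The cross-sectional figure of 320 offers partial support: (5 × 30 + 50) × 1.6 = 320. This leaves out one of the six 30-net surveys listed there; with all six, 230 × 1.6 = 368.

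The 200 is a real planning number. The cross-sectional paragraph assumes 3.2 nets per house, and 200 × 3.2 = 640, the additional nets stated. Then 1634 + 640 = 2274, in line with the stated total of 2300 per arm.

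**2. Does 200 leave 125 at 36 months?** Read the 20% as households lost from observation.

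| Month | 20% of those remaining each year | 20% of the starting number each year |
|---|---|---|
| 12 | 160 | 160 |
| 24 | 128 | 120 |
| 36 | 102.4 | 80 |

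The shortfall from 125 is about 23 to 45 households. Retaining 125 would take 245 (125 / 0.8³, rounded up) or 313 (125 / 0.4, rounded up).

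Read the 20% instead as net loss. Under Data analysis, missing nets go into the attrition numerator and stay in the denominator, so the attrition endpoint needs no inflation for them. The hole index does need surviving nets, so an allowance is legitimate for that outcome.

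**3. The 150.** The higher of two ID codes per house is one net per house: at most 125 nets from 125 houses, or 200 from 200. The stated 150 is neither, and it is 20% above 125 (150 / 125 = 1.2).

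**4. What sample supports 12 points?** The protocol gives no alpha, power, baseline or clustering allowance. I assume two-sided 5%, 80% power, independent nets, and a 36-month loss of 1 − 0.8³ = 48.8% in one arm. The detectable difference d = p₂ − p₁ solves

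d√n = 1.96 √[2p̄(1 − p̄)] + 0.84 √[p₁(1 − p₁) + p₂(1 − p₂)].

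- n = 250 (125 × 2): (1.379 + 0.588) / √250 = 12.4 points. Power for 48.8% against 60.8% is about 77%.
- n = 400 (200 × 2): (1.382 + 0.590) / √400 = 9.9 points. Power is about 93%.

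Two nets share a house. With an assumed within-house correlation of 0.1 to 0.5, the design effect 1 + ρ is 1.1 to 1.5, and solving again with n divided by it gives:

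- 250 nets: 13.0 to 15.2 points
- 400 nets: 10.3 to 12.1 points

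The Study design section gives all participating households in a hamlet the same net type, across eighteen hamlets. Clustering at that level would widen these figures further. Checking all household nets makes about 640 a third possible denominator.

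**5. Replacement.** The withdrawal rule covers owners who withdraw or move away with their nets, and it names no exception for the cohort. A substitute brought in late has been at risk for less time, if its net is new, or is by selection a net still in use. Either lowers observed attrition. The documents give no expected number of such replacements, so the bias cannot be sized.

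**The case against.** **No reserve is stated.** A reader might infer that the 75 extra households are kept to top up the 250 nets as they are lost, so that the 36-month survey would show only the last year's 20% loss instead of 48.8%. The documents do not support this. The 200 are said to participate and are supplied with nets as participants. Torn, discarded, sold or stolen nets are recorded as losses with reasons, not replaced. Data analysis divides missing nets by nets distributed. Even in a hypothetical full annual top-up (250 nets, 50 added at months 12 and 24, 50 lost each year), that estimator gives 150 / 350 = 43%, not 20%. This objection stands. What remains is the narrower written rule on withdrawals and movers.

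**Some inflation is proper.** Hole counts need nets still present, and the Discussion reports that families moving and seasonal absence cost an earlier Tanzanian evaluation power. This stands, so the 200 cannot be called needless outright. It still falls short of 125 at 36 months if the 20% is loss from observation.

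**No target of 125 at month 36 is written down, and the formula is inferred.** True. But 125 is the number said to be followed over 3 years, and no other purpose for the step from 125 to 200 is given.

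**Twelve points may be right.** With 250 independent nets the figure is 12.4; with 400 nets and a design effect near 1.5 it is about 12. Either could lie behind the claim. That is the difficulty: the two samples imply different assumptions, and the protocol fixes neither. The 93% power for 400 nets should not be relied on, because it ignores clustering.

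**Conclusion.** The concern holds as a conflict in stated figures. The protocol gives 125 and 200 households per arm for one cohort, leaves 75 without a stated role, and asks for 150 one-per-house nets where 125 houses can give at most 125. If the 20% a year is loss from observation, 200 leaves about 102 households at 36 months, or 80 under linear loss. If it is net loss, the allowance is not needed for the attrition endpoint, though it can be defended for hole counts.

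The 12-point figure cannot be tied to a sample. It is about 12.4 points with 250 nets and 9.9 with 400, and larger once household and hamlet clustering are allowed for. These values rest on my assumptions of two-sided 5%, 80% power, independence and 48.8% loss.

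The withdrawal rule, applied to the cohort, would bias attrition somewhat downward by an unknown amount. The documents do not support a claim that worn or discarded nets would be replaced, or that the true loss would be largely hidden. This should be corrected, but it does not undermine the design.

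**What to change.** 1. Reconcile 125 households with 250 nets, 200 households, and 150 fabric-integrity nets. State which households and nets form the cohort, using all households followed from distribution.
2. Fix that set at t0 as the denominator that Data analysis already calls for.
3. Exempt the cohort from the replacement rule for withdrawals and movers, and treat such nets as censored at the last visit at which they were observed.
4. Say separately what loss is allowed for household follow-up and what for nets surviving to a hole count.
5. Restate the 12-point difference for the cohort so defined, with alpha, power, assumed loss and design effect.

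The cost is wording and one recalculation; the households and nets are already in the plan. There is one limit. The trial is in monitoring year 2, so any of the 200 households not followed from distribution cannot be added to a t0 denominator now. In that case the smaller cohort, with its larger detectable difference, should be stated as it is. If all 200 were followed, presence must be recorded for at least 400 nets per arm, which the stated check of all household nets already covers.
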